## Abstract

**Background:**

Advances in multi-modality treatment of locally advanced rectal cancer (LARC) have resulted in low local recurrence rates, but around 30% of patients will still die from distant metastatic disease. In parallel, there is increasing recognition that with radiotherapy and systemic treatment, some patients achieve a complete response and may avoid surgical resection, including in many cases, the need for a permanent stoma. Extended neoadjuvant regimes have emerged to address these concerns. The inclusion of immunotherapy in the neoadjuvant setting has the potential to further enhance this strategy by priming the local immune microenvironment and engaging the systemic immune response.

**Methods:**

PRIME-RT is a multi-centre, open label, phase II, randomised trial for patients with newly diagnosed LARC. Eligible patients will be randomised to receive either: short course radiotherapy (25 Gray in 5 fractions over one week) with concomitant durvalumab (1500 mg administered intravenously every 4 weeks), followed by FOLFOX (85 mg/m^2^ oxaliplatin, 350 mg folinic acid and 400 mg/m^2^ bolus 5-fluorouracil (5-FU) given on day 1 followed by 2400 mg/m^2^ 5-FU infusion over 46–48 h, all administered intravenously every 2 weeks), and durvalumab, or long course chemoradiotherapy (50 Gray to primary tumour in 25 fractions over 5 weeks with concomitant oral capecitabine 825 mg/m^2^ twice per day on days of radiotherapy) with durvalumab followed by FOLFOX and durvalumab. The primary endpoint is complete response rate in each arm. Secondary endpoints include treatment compliance, toxicity, safety, overall recurrence, proportion of patients with a permanent stoma, and survival. The study is translationally rich with collection of bio-specimens prior to, during, and following treatment in order to understand the molecular and immunological factors underpinning treatment response. The trial opened and the first patient was recruited in January 2021. The main trial will recruit up to 42 patients with LARC and commence after completion of a safety run-in that will recruit at least six patients with LARC or metastatic disease.

**Discussion:**

PRIME-RT will explore if adding immunotherapy to neoadjuvant radiotherapy and chemotherapy for patients with LARC can prime the tumour microenvironment to improve complete response rates and stoma free survival. Sequential biopsies are a key component within the trial design that will provide new knowledge on how the tumour microenvironment changes at different time-points in response to multi-modality treatment. This expectation is that the trial will provide information to test this treatment within a large phase clinical trial.

*Trial registration*

Clinicaltrials.gov NCT04621370 (Registered 9th Nov 2020)

EudraCT number 2019-001471-36 (Registered 6th Nov 2020)

**Supplementary Information:**

The online version contains supplementary material available at 10.1186/s13014-021-01888-1.

## Background

Locally advanced rectal cancer (LARC), defined as stage II or stage III disease, constitutes up to one third of rectal tumours at diagnosis [1]. Treatment of LARC requires a multi-modality approach because surgical resection alone results in unacceptably high rates of local recurrence [2]. Radiotherapy is the main therapeutic modality currently used prior to surgery, delivered either as short course (5 × 5 Gray (Gy) over one week) (SCRT) or as long course radiotherapy with concurrent fluoropyrimidine chemotherapy (45–50 Gy over 5 weeks) (LCRT) [3, 4]. Leaving a ‘gap’ following radiotherapy allows for maturation of tumour regression and improves down-staging [5–7]. Increasingly, cytotoxic chemotherapy is being delivered in this gap, primarily to treat micro-metastatic disease and reduce distant recurrence [8, 9]. This strategy shows improved compliance and tolerability, and improved response rates compared to chemotherapy delivered in the adjuvant setting [10–12], even with intensification of the chemotherapy regimen [12].

Using this approach of sequential radiotherapy and chemotherapy prior to surgery, also known as total neoadjuvant treatment, some patients achieve a clinical complete response (cCR) to treatment and if monitored carefully, a select number of these good responders can avoid surgery altogether. The evaluation of cCR is usually performed at the end of treatment and defined as the absence of clinically detectable tumour using radiological evidence, clinical examination and endoscopic appearances [13]. Reports suggest that the proportion of patients achieving cCR after chemoradiotherapy in the order of around 15% [14, 15]. Pathological complete response (pCR) is confirmation of no viable tumour at resection for patients who do proceed to surgery [16]. Published series have demonstrated similar disease free survival (DFS) and overall survival (OS) for patients who have organ preservation after achieving a cCR compared to those who undergo surgery [17, 18], with 3 year colostomy free survival of up to 74% [18]. Unfortunately, approximately 20% of patients do not achieve any down-staging and, whilst the majority of patients have some response, most will still require surgery [15, 19, 20]. Given that only a minority of patients are achieving organ preservation with current treatments, intensification of neoadjuvant therapies is a primary research goal in rectal cancer [21].

There is a strong rationale for selecting immune checkpoint blockade as a candidate therapy for treatment intensification in this context. Previous use of immunotherapy in colorectal cancer has been mainly limited to the metastatic setting, where good responses are seen particularly in patients with deficiency in mismatch repair (MMR) proteins within the tumour [22–24]. Although MMR deficiency is only detected in a minority of patients with LARC, the neoadjuvant setting provides an opportunity to evaluate this treatment in both MMR proficient, as well as MMR deficient LARC. Specifically, DNA damaging treatments used in the neoadjuvant setting such as radiotherapy [25] and chemotherapy [26, 27] induce cellular damage and the resulting antigen exposure can incite lymphocytic responses. In this respect, radiotherapy and chemotherapy may ‘prime’ the tumour microenvironment, and when used in combination with immunotherapy may enhance this host anticancer immune response. In addition, recent evidence has suggested that moving immunotherapy earlier in the disease trajectory when tumour is in situ may improve response rates [28]. Given that immune checkpoint blockade acts systemically, by using immunotherapy for treatment of LARC there is also the potential to reduce distant micro-metastases. Indeed, this systemic effect of immunotherapy may be increased through the combination with radiotherapy in what is known as an abscopal effect [29].

The PRIME-RT trial will test the intensification of neoadjuvant treatment for patients with LARC using immune checkpoint blockade combined with radiotherapy and chemotherapy. The main aims of the PRIME-RT trial are:To test whether the addition of anti-PD1 immunotherapy to extended neoadjuvant regimens results in high rates of complete response that may enable a larger proportion of patients with locally advanced rectal cancer to have organ preservationTo evaluate the priming effect of adding chemotherapy and immune checkpoint blockade to patients receiving SCRT and those treated with LCRT.

## Methods/Design

PRIME-RT is an open label, multi-centre phase II randomised trial with 1:1 allocation between arm A and arm B (Fig. 1). The main trial will commence after completion of a safety run-in.

**Fig. 1 Fig1:**
[figure not shown]
Process of recruitment of patients to PRIME-RT and random allocation of patients between treatment arms

### Trial interventions

The treatment schema for each arm of PRIME-RT is outlined in Fig. 2. Arm A consists of SCRT, followed by up to six cycles of FOLFOX chemotherapy. Patients also receive concurrent durvalumab (anti-PD-1 immune checkpoint inhibitor), commencing in the week prior to radiotherapy and continuing until completion of FOLFOX chemotherapy. In Arm B, patients receive LCRT followed by up to four cycles of FOLFOX chemotherapy, alongside concurrent durvalumab as for Arm A. LCRT consists of 50 Gy delivered to the primary tumour and 45 Gy to the elective pelvic nodes, delivered over 25 fractions with concomitant capecitabine chemotherapy 825 mg/m^2^ orally twice daily on the days of radiotherapy. Regarding LCRT, 45 Gy in 25 fractions has been the standard, accepted dose in the UK for pelvic rectal radiotherapy for many years and was used in a recent, large phase III rectal cancer trial (ARISTOTLE), which employed 3D conformal radiotherapy as the treatment technique [30]. There is evidence of a dose related response for rectal tumours [31], which has led to increased interest in using boost doses to areas of primary tumour. It is now more feasible to deliver boost doses safely and efficiently with the use of intensity modulated radiotherapy (IMRT). The dose levels used in PRIME-RT align with recently published United Kingdom (UK) consensus guidance, which has suggested using 45 Gy to elective pelvic nodes and a 50 Gy boost to primary tumour [32, 33].

**Fig. 2 Fig2:**
[figure not shown]
Treatment schema for Arm A and Arm B of PRIME-RT

For both arms, FOLFOX consists of a 400 mg/m^2^ bolus of fluorouracil over 10–15 min followed by a 2400 mg/m^2^ fluorouracil given as a continuous infusion over 46–48 h starting on day 1. Folinic acid 350 mg flat dose is administered over 2 h, in addition to oxaliplatin 85 mg/m^2^ over 2 h, both on day 1. Durvalumab is delivered as 1500 mg intravenously over 60 min every four weeks for up to four cycles in both arms. Radiotherapy treatment is delivered using inverse planned IMRT.

### Trial population

The target population for the main PRIME-RT trial consists of adult (≥ 18 years), fit (ECOG Performance Status 0–1) patients with a LARC which can be encompassed within a radical radiotherapy field. One of the following disease related features must be present on magnetic resonance imaging (MRI) assessment: cT3b+, EMVI positive, primary tumour or morphologically malignant lymph node at 2 mm or less from the mesorectal fascia or beyond the mesorectal fascia or a low rectal tumour requiring abdomino-perineal excision (APE). Patients are not permitted to enter the trial if they have any degree of dihydropyrimidine dehydrogenase deficiency, have received previous pelvic radiotherapy or have a history of inflammatory bowel disease or active autoimmune disease. Systemic steroid therapy or any other form of immunosuppressive medication within 14 days prior to the first dose of trial treatment is not permitted.

The trial criteria for the safety run-in is identical to the main trial except that patients are permitted to have metastatic disease with a primary rectal tumour in situ and to have received prior chemotherapy, but not immunotherapy, for the current malignancy. Additional File 1 contains a full list of inclusion and exclusion criteria. Patients for both parts of the trial will be recruited in the hospital setting and identified as potential trial candidates via multi-disciplinary meetings. The trial opened on 15th January 2021 with the first patient recruited to the safety run-in cohort on 28th January 2021.

### Study objectives and end-points

The principal objective addressed in PRIME-RT is whether the addition of durvalumab and FOLFOX chemotherapy to radiotherapy in the neoadjuvant setting for patients with LARC improves response rates. Specifically, the primary endpoint is a measurement of the proportion of patients achieving either complete clinical or pathological response in each trial arm. Both clinical and pathological complete response are included to ensure that patients undergoing surgery, as well as those following an organ preservation strategy, will both contribute to assessment of the primary endpoint. Clinical response will be assessed using a combination of MRI, endoscopic and clinical examination as outlined in Additional File 2, with the European Society of Gastroenterology and Abdominal Radiology (ESGAR) template [34] used for MRI reporting.

Secondary objectives include evaluation of safety and tolerability of treatment, including quality of life and surgical morbidity. Quality of life will be assessed at baseline and months 3, 6, 12, 18, 24 and 30 using three validated questionnaires (European Organization for Research and Treatment of Cancer Quality of Life Core Questionnaire 30, the European Organization for Research and Treatment of Cancer Quality of Life Questionnaire-Colorectal Cancer 29 and the Euro Qol-5 dimensions 3 levels survey). Treatment efficacy will be measured using additional secondary endpoints such as the neoadjuvant rectal score (NAR), MRI-confirmed tumour regression or near tumour regression or any degree of down-staging. Longer-term outcomes such as overall relapse rates and survival will also be measured.

CD3 + T-lymphocyte concentration is the main translational end-point for the trial and will be used to investigate the extent of immune activation within rectal biospecimens before, during (week 2 and 6) and after treatment. Biopsy assessment of CD3 + will be determined in tumour tissues by immunohistochemistry and divided into two groupings as none/low vs moderate/high based on previous descriptions [35–37] and treatment will be considered to be effective if a moderate-high CD3 + infiltrate is seen in 40% of patients.

Exploratory objectives for the PRIME-RT trial will include evaluation of biomarkers of treatment resistance and response to immunotherapy-radiotherapy combinations, assessment of the molecular characteristics of rectal cancers in which an immune priming response is achieved, and an analysis of how these responses may differ with respect to MMR status. The schedule for collection of data for the purposes of assessing all trial end-points is detailed in Additional File 3.

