### Analysis plan and sample size calculation

Efficacy analyses will be on an intention to treat basis and safety analyses will include all patients who start treatment. For the primary efficacy analysis, a one-sided 80% confidence interval for the proportion of patients in each arm who have a complete response will be calculated using the Clopper–Pearson [39] approach. In each arm, treatment will be considered effective if at least five patients have a complete response. This pre-defined end-point for both trial arms is based on a hypothesis that complete response rates at six months will exceed 30% compared to rates of approximately 15% for standard long course chemoradiotherapy (LCRT) [14, 15]. If at least five patients in an arm have a complete response rate (equating to a success rate of 23.8%, with a lower one-sided 80% confidence limit of 15.1%), the hypothesis that the true efficacy is ≤ 15% is rejected. If the true complete response rate is 30% (the hypothesised level of efficacy used for the primary endpoint calculation), 21 patients per arm provides 80% power to demonstrate that the one-sided 80% confidence interval (20% 1-sided level of statistical significance) for the complete response rate excludes 15% (the minimum level of efficacy to warrant further evaluation).

If both arms appear to be equally effective, the main secondary endpoint (occurrence of Grade 3–5 treatment-emergent and treatment-related adverse events) will be used to determine the most appropriate trial arm to take forward for further study. The null hypothesis is that 50% of patients will not experience any Grade 3–5 toxicity, with an alternative hypothesis that 78% of patients will not experience any Grade 3–5 toxicity. If at least 14 participants in an arm experience no Grade 3–5 toxicity, (equating to a no toxicity rate of 66.6%, with a lower one-sided 90% confidence limit above 50%), the null hypothesis (that the true “no Grade 3–5 toxicity” rate is ≤ 50%) will be rejected in favour of the alternative hypothesis that the “no Grade 3–5 toxicity” rate is 78%. For the secondary endpoint calculation, 21 patients per arm provides 90% power to demonstrate that the one-sided 90% confidence interval (10% 1-sided level of statistical significant) for the “no Grade 3–5 toxicity” rate excludes 50%.

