If both trial arms achieve a complete response rate of over 30% and demonstrate low toxicity as described above, a tiered consideration of other endpoints will be used to decide which treatment strategy to use moving forwards. In order of decreasing importance, these factors are; toxicity, absolute percentage of patients with complete response, surgical morbidity, the NAR score, local regrowth (36 months), overall survival (36 months), recurrence free survival (36 months), quality of life, percentage of patients with high grade CD3 + or a fold change in CD3 + compared to baseline.

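### The main translational endpoint, serial CD3+ concentration, is judged on a two-group split that ignores each patient's baseline and so discards information on immune priming

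*Protocol article*

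**What the plan says.** Under Study objectives and end-points, the protocol article states that "CD3 + T-lymphocyte concentration is the main translational end-point for the trial". Biopsies are taken "before, during (week 2 and 6) and after treatment", to study how far the immune response is activated. CD3+ is measured by immunohistochemistry and then "divided into two groupings as none/low vs moderate/high based on previous descriptions". Treatment counts as effective on this endpoint if a moderate/high "infiltrate is seen in 40% of patients". No time point, null rate, alpha, interval or baseline comparison is attached to that rule.

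Under Analysis plan and sample size calculation, CD3+ comes last of nine tiered factors for choosing between two successful arms. It is worded there as "percentage of patients with high grade CD3 + or a fold change in CD3 + compared to baseline". The sample size of 21 per arm is justified for complete response and for freedom from Grade 3–5 toxicity. It is not justified for CD3+.

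The Background lists evaluation of the priming effect in each radiotherapy schedule as one of two main aims. Trial design and analysis plan rules out comparative analyses between arms.

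**The concern.** Priming is a change within a patient. The design collects what is needed to see it, namely repeated biopsies with a pre-treatment reference, but the success rule uses neither the quantity nor the change. A tumour whose CD3+ density rises several-fold but stays in the none/low group scores the same as one that does not move. A tumour just below the cut that drifts over it scores as a full success. One that was already moderate/high before treatment also counts towards the 40%.

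Each arm stands alone with at most 21 patients, so there is little information to spare. At stake is the conclusion on the priming aim, and what is carried into a later trial about how each radiotherapy schedule affects the immune microenvironment.

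**Working it through.** **Inputs from the article.** 21 patients per arm; 40% moderate/high as the success level; one-sided 20% level for complete response and one-sided 10% for toxicity.

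**Assumptions (not in the article).** Log CD3+ density is normal with equal SD before and after; within-patient correlation is 0.5; all 21 pairs are evaluable; the true moderate/high share rises from p0 at baseline to 40%.

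**1. The plan's own figures.** The article says "21 patients per arm provides 80% power to demonstrate that the one-sided 80% confidence interval" excludes 15%, with a rule of at least 5 responders. Exact binomial: P(X ≥ 5 | 21, 0.15) = 0.197 and P(X ≥ 5 | 21, 0.30) = 0.802. The lower one-sided 80% Clopper–Pearson limit for 5/21 is 15.07%. The stated figures reproduce, but they concern complete response only.

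**2. The 40% rule as written, read per arm.** 0.40 × 21 = 8.4, so 9 patients are needed. P(X ≥ 9 | 21, p) is 0.15 at p = 0.30, 0.48 at p = 0.40 and 0.81 at p = 0.50. The two-sided 95% interval for 9/21 is 22% to 66%.

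**3. Information kept after the cut.** For a normal variable with a share q above the cut c, the relative efficiency is φ(c)² / [q(1 − q)].
- q = 0.50: 0.3989² / 0.25 = 0.64, and 21 × 0.64 ≈ 13 patients
- q = 0.40: 0.62, about 13 patients
- q = 0.30: 0.58, about 12 patients
- q = 0.20: 0.2800² / 0.16 = 0.49, and 21 × 0.49 ≈ 10 patients

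**4. Shift implied by the rise to 40%, in SD units.** δ = z(1 − p0) − z(0.60).
- p0 = 15%: 1.036 − 0.253 = 0.783
- p0 = 20%: 0.842 − 0.253 = 0.588 (from unrounded z values)

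At correlation 0.5 the SD of the change is √[2(1 − 0.5)] = 1. The paired-t non-centrality is therefore δ√21, which is 3.59 and 2.70. With 20 degrees of freedom, power at one-sided 10% is 0.987 and 0.913.

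**5. Paired comparison.** McNemar power is by simulation and repeats to within about one point.

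| One-sided level | p0 | Paired t | Exact McNemar | Mid-p McNemar |
|---|---|---|---|---|
| 10% | 15% | 99% | 66% | 79% |
| 10% | 20% | 91% | 48% | 62% |
| 20% | 15% | 100% | 84% | 91% |
| 20% | 20% | 97% | 68% | 80% |

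**6. Against a one-sample exact binomial at one-sided 10%**, the form of rule the plan uses for its other binary endpoints:
- p0 = 15%: the threshold is 6 of 21 (actual size 0.083) and power is P(X ≥ 6 | 21, 0.40) = 0.90, against 99% for the t-test.
- p0 = 20%: the threshold is 8 of 21 (actual size 0.043) and power is 0.65, against 91%.

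At p0 = 20% the actual size is well below 10%. Part of that gap therefore comes from the discreteness of the exact test and not from the loss of scale.

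**7. Sensitivity.** At one-sided 10%, over correlations 0 to 0.7 and p0 from 10% to 25%, the paired gain is 13 to 55 points against exact McNemar and 6 to 40 against mid-p. With 16 evaluable pairs and p0 = 20%, power is 84% against 34% (mid-p 50%). The continuous analysis had more power in every setting tried.

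**The case against.** The strongest reply is that the lost power belongs to tests the article does not contain. It states a responder rule, which asks how many patients reach an infiltrated state. That is a different question from the mean change, so replacing it changes the estimand as well as the efficiency. This stands in part. It is why the size of the loss is conditional and why the responder percentage should be kept.

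A reader might infer that the two-group split is the only CD3+ analysis planned. The documents do not support that: the arm-selection list includes "or a fold change in CD3 + compared to baseline", and modelling detail may sit in an analysis plan that is not shown. But that entry is an alternative inside the last-ranked factor, used only if both arms succeed, and it does not alter the success rule.

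A reader might also infer that a real rise will probably be missed. That does not follow. At a baseline share of 15%, a one-sample exact rule keeps 90% power at one-sided 10%, and exact McNemar keeps 84% at one-sided 20%.

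Two further points stand. The article implies a quantitative CD3+ value, through its words concentration and fold change, but never confirms that a density is recorded for every biopsy. The cut has cited sources, so it serves comparability with earlier work, and the absence of a regulatory requirement for it is not a fault.

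**Conclusion.** The concern holds in a limited form. The success criterion for the main translational endpoint is fixed on a two-group scale without reference to baseline, although the aim is to detect change and the biopsies to measure it are being taken. Under normality the binary scale keeps about half to two-thirds of the information (0.49 to 0.64).

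In power terms, the loss at p0 = 15% to 20% runs from 9 points (one-sample exact rule, one-sided 10%, p0 = 15%) to 43 points (exact McNemar, one-sided 10%, p0 = 20%). These sizes rest on assumed normality, correlation, baseline share and alpha, none of which the article gives for CD3+. The direction was the same in every setting tried.

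The effect is confined to the translational aim. The complete response result, the toxicity rule and the sample size are untouched.

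**What to change.** For each arm, make within-patient change from the pre-treatment biopsy the main analysis of CD3+.

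- If a density is recorded, analyse the change in log density. Report the geometric mean ratio with a confidence limit, use a Wilcoxon signed-rank test as a check, and state the offset used for zero counts.
- If only grades are recorded, analyse the full ordinal grade with a signed-rank or ordinal method.
- Keep the moderate/high percentage and the 40% figure as a responder summary, with its confidence interval, for comparison with the literature.
- Use the same fold-change measure as the CD3+ factor in the arm-selection list.

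The cost is wording and a modest amount of extra analysis, with no additional patients or biopsies. The downsides are that the 40% figure becomes supportive, and that zero counts and post-treatment samples without tumour need a stated handling rule.
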